Alternative tobacco products to conventional cigarettes have come on the global market with claims of being “modified risk” tobacco products. These electronic devices heat the tobacco instead of burning it to supposedly deliver fewer toxins than cigarette smoke. These heated tobacco products include HeatSticks, a specially designed heated tobacco unit that contains tobacco heated up to 350˚C by the iQOS device. The product was developed by Philip Morris International, Inc, which claims that the vapor from HeatSticks heated by the iQOS device contains 90%-95% less harmful and potentially harmful compounds and is 90%-95% less toxic than the smoke of a reference combustible cigarette. Results of a 3-month reduced-exposure study in Japan showed that a reduction in 15 biomarkers of exposure to 15 harmful and potentially harmful compounds for the smokers who switched to a heated tobacco product for the duration of the study approaches the reduction in the same biomarkers for smokers who quit for the duration of the study [14]. Polosa et al showed that electronic cigarettes (ie, a battery-operated device that emits doses of vaporized nicotine) might improve COPD outcomes, including subjective respiratory outcomes as well as annual exacerbation rate [15]. We hypothesize that participants who use iQOS with HeatSticks will have less prevalent presence of respiratory symptoms, have better functional exercise capacity, and experience fewer exacerbations compared to those who smoke combustible cigarettes.

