The inclusion of secondary endpoints (eg, lab tests, ECG, and clinical assessment) allows for generating further hypotheses for different effects of switching to iQOS. Schedule of enrollment, data collection, and assessment are shown in Tables 2 and 3.

All study participants in both cohorts will receive smoking cessation advice according to clinical standards endorsed by Kazakhstan’s Health Ministry, offered throughout the study at each visit. The participants will also be offered formal professional assistance on smoking cessation. At the screening visit, in conjunction with signing the informed consent form, clinical investigators will give smoking cessation advice. It will be free of charge (paid by the sponsor) and is set out in the informed consent form. It will include psychological support to eliminate nicotine dependency, and participants will be referred to a specialist commercial medical organization in Almaty. We anticipate that some smokers and iQOS users will quit and that some smokers will switch to a reduced-risk product during the study. Quitting and switching will not be considered as reasons for early withdrawal and will be accounted for in sample size calculations.

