### Computer-Assisted Personal Interviewing

KAPM has developed an electronic data capture system in the form of its proprietary computer-assisted personal interviewing app. The app is available for tablet personal computers and will be modified to be implemented in the cohort study to collect, store, and transmit data related to a personal survey interview. The questionnaire will be designed to collect data on possible COPD risk factors including history of smoking, current smoking, level of smoking exposure (in pack-year), passive smoking, occupational and environmental hazards, including dusts, chemicals, and indoor fuel pollution. The questionnaire will contain covariates: age, gender, ethnicity, education, occupation, and self-reported morbidity. It will also include questions to address COPD exacerbations and to record the use of combustible cigarettes, iQOS with HeatSticks, electronic cigarettes, and other alternatives, as well as iQOS switch date.

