We will apply a three‐stage reporting framework [27]. Model 1 will report the crude analysis (without any adjustments for confounders), Model 2 will report the semi‐adjusted analysis (including the following a priori defined covariates of gender, age, number of pack-year at base-line), and Model 3 will present the fully adjusted model (including all the covariates as in Model 2 plus those covariates that have discrepancies across two cohorts and change the estimate of association). The matching variables can be ignored in the model if we have exactly two controls for each participant in the iQOS cohort. Because of dropouts and other reasons, that will be impossible to achieve. There will be some confounder effect remaining, which means we have to include matching variables in the analysis. Model diagnostic plots will be generated to test model assumptions, for example, normality of deviance residuals.

We will also use two methods of propensity score analysis (PSA)—stratification on the propensity score and inverse probability weighting using the propensity score [28]—to adjust for confounders that may vary in study groups.

For missing data analysis, we will use missing at random assumptions. Missing values will be handled by multiple multivariate imputation in R. We will analyze five copies of the data, each with missing values imputed, in the GEE/GLMM multivariate analysis. The estimates of association will then be averaged according to Rubin’s rule [29] to produce a single mean estimate and adjusted standard errors.

To address dual usage, switching, and quitting, we will use several methods. First, we will implement the intention-to-treatment strategy, that is, we will adjust only for baseline confounders and evaluate the exposure effect as if all study participants remain under the exposures at the baseline until end of follow‐up. Second, we will evaluate the exposure effect censoring switchers and quitters from the analysis. Third, particularly for dual usage, we will model two exposures, iQOS and conventional cigarette usage, as weighted sums of doses calculated in pack-years. Weights will depend on the importance of the different periods, where the closest period will have the highest weight.

Analysis will be done using R [19]. The Bonferroni correction of the significance level will be applied to account for three confirmatory hypotheses being tested in the study, so an alpha <.017 (0.05/3) will be considered significant.

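### The supplementary dose model carries only iQOS and cigarette terms, so use of a third product is invisible to it and a mover to e-cigarettes is coded like a quitter with the same history

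*Protocol article*

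**What the plan says.** The Statistical Analysis and Data Management Plan section of the protocol article opens the topic with "To address dual usage, switching, and quitting, we will use several methods". Three methods follow. The first keeps every participant in the baseline exposure group to the end of follow-up. The second censors switchers and quitters. The last is introduced by "Third, particularly for dual usage" and reads: "we will model two exposures, iQOS and conventional cigarette usage, as weighted sums of doses calculated in pack-years". On the weights it adds: "Weights will depend on the importance of the different periods, where the closest period will have the highest weight".

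The data collected are wider than the two exposures modelled. Under Computer-Assisted Personal Interviewing, the questionnaire is to "record the use of combustible cigarettes, iQOS with HeatSticks, electronic cigarettes, and other alternatives, as well as iQOS switch date".

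The article also expects use to change. The Recruitment section anticipates quitting in both cohorts and that "some smokers will switch to a reduced-risk product during the study". The Sample Size Calculation section allows for moves between tobacco products, for quitting and for concurrent use of several products. The Introduction cites a study suggesting that e-cigarettes "might improve COPD outcomes, including subjective respiratory outcomes as well as annual exacerbation rate".

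Nowhere does the article enter use of e-cigarettes or other products as an exposure or as a time-varying covariate.

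**The concern.** Of the three methods, the dose model is the only one that represents changing product use during follow-up. It does so with two terms. Someone who leaves cigarettes for a product that is neither cigarettes nor iQOS stops adding to the cigarette sum and adds nothing to the iQOS sum. The model cannot tell that person from one who stopped using everything. Someone who adds a third product to iQOS or cigarettes looks exactly like someone who did not.

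Because the closest period has the highest weight, current third-product use is left out where the model is most sensitive. By the Introduction's own account, e-cigarettes may bear on respiratory symptoms and exacerbations, which are close to two of the three primary outcomes. At stake is how the cigarette and iQOS dose slopes, and the comparison between them, can be read in a harm-reduction argument.

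**Working it through.** The article gives no figure for this point, so there is none to reproduce. The check is whether the coding follows from the text, and under what conditions it matters.

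**1. Coding of product histories.** For each product, dose D = Σ w(t)·x(t), where x(t) is use in period t and w(t) is the period weight. The article gives no numerical weights. For illustration, assume five yearly follow-up periods, weights 1/15, 2/15, 3/15, 4/15 and 5/15, and use of one pack (or equivalent) a day.

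| History | Cigarette dose | iQOS dose |
|---|---|---|
| Smokes years 1–2, then quits | (1+2)/15 = 0.20 | 0 |
| Smokes years 1–2, then e-cigarettes | (1+2)/15 = 0.20 | 0 |
| Smokes years 1–2, then iQOS | (1+2)/15 = 0.20 | (3+4+5)/15 = 0.80 |
| Smokes throughout | 15/15 = 1.00 | 0 |

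The first two rows are identical. This does not depend on the assumed weights: the third product has x(t) = 0 in both sums for every t, so any weights give the same pair.

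**2. When the slopes are biased.** Suppose the linear predictor should contain b_c·D_c + b_i·D_i + g·Z, where Z is third-product use and g its effect compared with non-use at the same two doses. Leaving Z out gives, approximately, slopes b_c + g·d_c and b_i + g·d_i, where d_c and d_i are the coefficients of Z regressed on the two doses. Bias therefore needs g ≠ 0 and Z related to at least one dose. If third-product users have the same outcomes as quitters with the same history, g = 0 and the bias vanishes. The article gives neither g nor the frequency of Z, so no slope bias can be computed.

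**3. A rough sense of scale, on assumed values.** The Sample Size Calculation section gives CAT ≥10 prevalences of 17% (ex-smokers) and 42.8% (current smokers) and an odds ratio of 0.27. Check: (0.17/0.83)/(0.428/0.572) = 0.274.

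Suppose a share f of the people with no current cigarette or iQOS use are e-cigarette users, whose prevalence p_e lies a fraction r of the way from 17% to 42.8% on the logit scale. The mixed prevalence is (1−f)·0.17 + f·p_e.

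- f = 10%, r = 0.25: odds ratio against smokers 0.28.
- f = 25%, r = 0.5: p_e = 0.281, mixed prevalence 0.75·0.17 + 0.25·0.281 = 0.198, odds ratio 0.33.
- f = 50%, r = 0.75: odds ratio 0.47.
- r = 0 (e-cigarette users resemble quitters), any f: odds ratio stays at 0.27.

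This is a two-group contrast, not a slope of the planned model. It shows only that mixing can be negligible or material depending on two unknowns.

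**4. Whether another part of the plan closes the gap.** The first method ignores post-baseline use by design. The second drops switchers and does not model their exposure. Model 3 admits covariates that differ between cohorts, judged at baseline, and that change the estimate; uptake during follow-up does not enter that way. The cohort-definition sensitivity analysis varies only the percentage of iQOS use.

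**The case against.** The strongest reply concerns reach. The three methods share the task, and the dose model is aimed mainly at dual use. The confirmatory focus is the time-by-group interaction between the two cohorts. The baseline-exposure analysis is untouched, and censoring switchers, on the ordinary meaning of the word, removes a smoker who moves fully to e-cigarettes (the article does not define a switcher). All of this stands and limits the importance of the point.

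The expectation of third-product use is also less specific than it may look. The reduced-risk product in the Recruitment section is not named and could be iQOS, and the Sample Size Calculation section speaks of tobacco products. The article does not predict substantial movement to e-cigarettes. That stands too, although it has chosen to record such use.

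A further reply is that a full analysis plan, not shown, might add a covariate. That is possible, but the article itself fixes the number and identity of the modelled exposures at two, so this is more than a detail left open.

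A reader might infer three stronger things that the text does not support:

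- That an iQOS user who adds e-cigarettes is coded as cutting down. The iQOS dose falls only if iQOS use falls; the added use is simply ignored.
- That quitters and e-cigarette users form a group with zero on both terms. The doses are weighted sums over periods, and the quitter above has 0.20, not zero.
- That the odds ratios in the working measure the model's bias. They rest on assumed uptake and effect and describe a contrast that this model does not estimate.

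**Conclusion.** The point holds for the dose model alone. It follows from the text, whatever the weights, that a mover to a third product and a quitter with the same earlier cigarette and iQOS history receive the same dose pair, and that added third-product use is not represented. The cigarette and iQOS slopes can be biased if third-product use affects the outcomes relative to non-use and is related to the doses. The article supplies neither quantity, so size and direction are unknown, and the bias is nil if such users resemble quitters.

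It would be tempting to conclude that the confirmatory comparison, or the whole handling of switching and quitting, is compromised. The article does not support that: the baseline-exposure analysis does not use these doses, and the censoring analysis probably removes full movers. This is a modest but real weakness in a supplementary analysis, worth correcting because the data are to be collected anyway.

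**What to change.** Add to the dose model a time-varying term for e-cigarettes and other tobacco or nicotine products, taken from the questionnaire data. Use a recency-weighted amount where one can be formed, and an any-use indicator by period where no pack-year equivalent exists. The aim is that post-baseline non-use is distinguished from use of another product; it is not to create a group with zero on every term.

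The cost is one extra term in a model already planned, with no new data collection. The downside is slightly less precision for the other two slopes, or a sparse and poorly estimated term, if third-product use turns out to be rare.

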## Methods

### Study Design

The goal of this study is to evaluate whether the presence of respiratory symptoms, functional exercise incapacity, and COPD exacerbation rate across time are the same between the exposure group (users of iQOS with HeatSticks) and the control group (smokers of combustible cigarettes) through hypothesis testing.

In addition to this confirmatory goal, we would like to explore trends in spirometry results, chest CT scan results, prevalence of impaired quality of life, metabolic syndrome, abnormalities found by electrocardiography (ECG), physical exams, and serum lab tests among those who use iQOS with HeatSticks and those who currently smoke combustible cigarettes.

Exacerbation history will be collected prospectively (every 3 months) with the use of the adapted version of our proprietary SymptoMaster (Web, iOS, and Android) [16], and Medintel (Web) apps [17]. Symptoms history will be analyzed by clinical investigators. Should there be symptoms identified that are relevant to COPD, clinical investigators will approach health care organizations (serving participants in primary health care catchment area) to obtain ambulatory records of the use of antibiotics and/or systemic glucocorticoids or a health care utilization event.

Our primary confirmatory outcome variables are (1) presence of respiratory symptoms defined by CAT≥10, (2) functional exercise incapacity, and (3) exacerbation rate. The main exposure variable is smoking status (users of combustible cigarettes and users of iQOS with HeatSticks). The study groups are defined as:

Individuals (men and women) aged 40-59 years (inclusive) with a minimum of 10 pack-year smoking history who switched to and predominantly use the heated tobacco product iQOS with HeatSticks (exposure group). Predominant use of iQOS with HeatSticks is defined as >70% use.Individuals (men and women) aged 40-59 years (inclusive) who are currently smoking combustible cigarettes with a minimum of 10 pack-year smoking history (control group)

Pack-years will be calculated by taking the average number of cigarettes smoked per day divided by 20 and multiplied by the number of years smoked.

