At the final visit, the odds ratio of association between the exposure and CAT score of ≥10 will equal 0.27 and a CAT ≥10 prevalence will be 42.8% in the control group.At the final visit, odds ratio of association between the exposure and inability to walk 450 meters on the 6MWT will equal 0.62 and a 6MWT <450 meters prevalence will be 16.7% in the control group.At the final visit, rate ratio of association between the exposure and exacerbations will equal 0.5 and annual exacerbation rate will be 0.1 in the control group based on conservative estimations from Woodruff et al [10]. We also assume that these associations will increase steadily from 1 to the above-indicated values. Sample size calculations for three primary confirmatory outcomes have been performed by simulations and the frequentist method based on the power and level of significance of a test. For each primary confirmatory outcome, we have generated data from the distribution assumed for the combustible cigarette smokers and the distribution for the iQOS with HeatSticks smokers (based on our assumptions of how their changes in respiratory symptoms prevalence, proportions of participants who walk less than 450 meters, and annual exacerbation rate might be different if switched from combustible cigarettes to iQOS with HeatSticks). We have used R [19] for simulations (1000 simulations per each primary confirmatory outcome variable) and fitting a generalized linear mixed-effects model (GLMM) on simulated data (function “glmer” in the package “lme4”). For sample size calculation, we have used a power value of 80%, two-sided significance level (alpha) 1.7% that accounts for multiple hypotheses testing, and 1:2 ratio for sample sizes of the experimental and control cohorts.

Then, we have adjusted the sample size for anticipated proportion of dropouts (taking into consideration a 10% annual dropout rate and the fact that already collected data relating to any participant who stops the study early will be analyzed). Sample size calculations are presented in Table 1.

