### Statistical Analysis and Data Management Plan

Appropriate descriptive statistics will be used to summarize required study elements overall and by cohort (eg, proportion, mean, standard error, median, and interquartile ranges). Exploratory graphical analysis will be done preliminary to numerical analysis. Histograms, two-dimensional scatterplots of raw data, will provide information on the univariate and bivariate distributions of the variables focusing on distribution of variables, relation between the variables, whether it is linear or nonlinear, etc. In addition, preliminary graphs will screen raw data by highlighting obvious data errors. Spaghetti plots, scatterplots of dependent variable scores versus the time variable with a separate line for each person, will explore likely models, especially whether effects are linear or not.

Generalized estimating equations (GEE) and GLMM will be used to assess the effect of exposure on outcome variables. Both GEE and GLMM are used to account for within-person correlation of observations due to repeated measures. GEE uncovers the population average effect of a covariate, whereas GLMM estimates the individual specific effect. For binary confirmatory outcomes, CAT score ≥10, and inability to walk 450 meters on the 6MWT, the logit transformation will be utilized as the model link function. To model the annual exacerbation rate (count data), we will use the logarithm transformation and the Poisson or quasi-Poisson distribution depending on mean-variance relationship.

Presence of the statistically significant “time by group” interaction coefficient in GEE/GLMM will be our focus. It will demonstrate that the primary outcomes in two cohorts will have been changed significantly and provide statistical evidence for the harm reduction hypotheses.

To adjust for confounders, we will examine distributions of all covariates in the exposed and control group and will use Cohen effect sizes [26] to identify whether participants’ characteristics are different between groups at baseline. The impact of a potential confounder will be confirmed on whether the adjustment for the confounding variable changes the estimate of association.

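### Bonferroni at 0.05/3 is valid, but Holm's step-down keeps the same 5% family-wise error and would raise power for the walk-test and exacerbation outcomes at almost no cost

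*Protocol article*

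**What the plan says.** Study Design fixes three confirmatory outcomes: "Our primary confirmatory outcome variables are (1) presence of respiratory symptoms defined by CAT≥10, (2) functional exercise incapacity, and (3) exacerbation rate". The Statistical Analysis and Data Management Plan section sets the multiplicity rule: "The Bonferroni correction of the significance level will be applied to account for three confirmatory hypotheses being tested in the study". Each test is then judged against .017, which the section derives as 0.05/3. Sample Size Calculation uses the same level, a "two-sided significance level (alpha) 1.7% that accounts for multiple hypotheses testing", with 80% power per outcome and a "1:2 ratio for sample sizes of the experimental and control cohorts".

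Table 1 gives the exposed/control numbers before and after dropout: CAT 23/46 and 31/62; 6MWT 260/520 and 347/694; exacerbations 255/510 and 340/680. The largest of these gives the stated total of 1041, and 400/800 are to be recruited.

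On the test itself, the analysis section says: "Generalized estimating equations (GEE) and GLMM will be used to assess the effect of exposure on outcome variables". It makes the interaction of time with group the coefficient of interest, in either estimator. It also describes three reporting models, two propensity score methods and three ways of handling switching, quitting and dual use. Before modelling, individual outcome plots "will explore likely models, especially whether effects are linear or not".

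**The concern.** With three hypotheses at a fixed 0.05/3, a rejection on one outcome brings no relief for the others. Holm does give that relief at the same family-wise error. It matters more than usual in this study because one of the three outcomes is far overpowered at the sample size set by another. The power forgone is on 6MWT and exacerbations, the two outcomes that determine the sample size.

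A secondary matter is that either procedure delivers its 5% only if one p-value per outcome enters it. The article names the outcome and the coefficient, but not the estimator, model stage or exposure strategy. It also states that GEE and GLMM estimate different effects, population-average and individual-specific.

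**Working it through.** **1. The plan's own figures.** 0.05/3 = 0.01667, printed as .017. Taken literally, 3 x .017 = 0.051. Table 1's dropout step is division by 0.75: 260/0.75 = 347 and 520/0.75 = 694, total 1041; 255/0.75 = 340; 23/0.75 = 31. All reproduce. The unadjusted 23, 260 and 255 come from simulations whose within-person correlation is not given. They cannot be checked and are taken as stated.

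**2. Noncentrality implied by 80% power at two-sided 0.05/3.** d = z(1 - 0.05/6) + z(0.80) = 2.394 + 0.842 = 3.236.

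**3. CAT at the size set by 6MWT.** With 260 exposed analysed against 23 needed, d = 3.236 x sqrt(260/23) = 10.9, so power is essentially 100%. Holm then tests the other two p-values at .025 (smaller) and .05 (larger).

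**4. Holm power at Table 1's numbers, two remaining outcomes independent.**
- At .025: Phi(3.236 - 2.241) = 0.840. At .05: Phi(3.236 - 1.960) = 0.899.
- These are the two steps, not Holm's power. An outcome is rejected if p < .025, or if p < .05 and the other outcome has p < .025: 0.840 + (0.899 - 0.840) x 0.840 = 0.89.
- Both rejected: 0.899^2 - (0.899 - 0.840)^2 = 0.80. Bonferroni: 0.80 x 0.80 = 0.64.

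**5. The same at the recruited size.** Table 1's factor gives 0.75 x 400 = 300 and 0.75 x 800 = 600 retained. For 6MWT, d = 3.236 x sqrt(300/260) = 3.476; for exacerbations, d = 3.236 x sqrt(300/255) = 3.510. From unrounded values:

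| | Bonferroni | at .025 | at .05 | Holm |
|---|---|---|---|---|
| 6MWT | 0.860 | 0.891 | 0.935 | 0.931 |
| Exacerbations | 0.868 | 0.898 | 0.939 | 0.935 |
| Both | 0.746 | | | 0.877 |

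**6. Dependence and error.** The correlation between outcomes is not given. For assumed values of 0 to 0.6, simulation at Table 1's numbers gives Holm power of 88-89% per outcome. Power for all three is 80-83%, against 64-70% under Bonferroni. With all nulls true, the family-wise error is the same for both rules (0.049 at correlation 0, 0.042 at 0.6). With CAT truly different and the other two null, it is 0.033 for Bonferroni and 0.049 for Holm, so both stay within 0.05.

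**7. If more than one test per outcome could be claimed.** Take k equicorrelated normal tests per outcome at 0.05/3, with three independent outcomes. Let p be the chance that at least one of the k is falsely significant; the family error is 1 - (1 - p)^3. For k = 1 this is 1 - (1 - 0.01667)^3 = 4.9%. The correlation r between the tests is not given, so a range is shown.

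| Tests per outcome | r = 0.98 | r = 0.8 |
|---|---|---|
| 2 | 6.0% | 7.9% |
| 3 | 6.6% | 10.2% |
| 6 | 7.6% | 14.9% |

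**The case against.** Bonferroni is fixed in advance, is valid under any dependence, and is the level at which the study was sized. The article claims at least 80% power per outcome, and on its own assumptions the rule delivers that. Bonferroni also gives simple simultaneous confidence intervals, which Holm does not. All of this stands. A reader might infer that the multiplicity rule is wrong or that the study misses its power target, but the document supports neither reading.

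Nor may the gain be stated by combining CAT's power at 400/800 with 80% for the other two outcomes, because 80% belongs to Table 1's smaller numbers. At 300/600 the baseline is already 86-87% and the gain per outcome is about 7 points. The article reserves the surplus recruitment for switching, quitting, dual use and confounding, so the effective size may lie between the two cases.

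On which test carries the threshold, a reader might multiply estimators by models by switching strategies and treat every cell as a confirmatory claim. The text does not support that. Models 1 to 3 are a reporting framework, and the article says the matching variables must be included, which argues against the crude model as the confirmatory one. The comparison of GEE, GLMM and propensity methods is listed as sensitivity analysis. The third switching method models weighted doses, so it does not yield the coefficient of interest. No sentence says that any significant result will be claimed. Naming the primary estimator, model and exposure strategy is also commonly left to a statistical analysis plan, which is not shown here. What remains is that the article itself designates no single test; sizing by GLMM and listing the baseline-exposure strategy first are hints only.

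**Conclusion.** The point stands as an inexpensive gain in efficiency, not as a correction of an error. Replacing Bonferroni by Holm adds about 9 percentage points of power for each of 6MWT and exacerbations at Table 1's numbers, or about 7 points at 300/600 retained. It adds about 16 points (64% to 80%) or 13 points (75% to 88%) for showing both.

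These sizes rest on the plan's effect assumptions, on Table 1's unadjusted numbers, on normal test statistics, and on independence of the two outcomes; correlation up to 0.6 changes the per-outcome figure by about one point. They also need CAT to be rejected. If it is not, Holm still never rejects less than Bonferroni. If all three outcomes had only 80% power, simulation gives 86-88% each under Holm.

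The naming of one test per outcome is a supporting step. The error figures in the last table apply only if several tests could each support a claim, and they depend on a correlation that the document does not give.

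**What to change.** In the Statistical Analysis and Data Management Plan section, replace the Bonferroni sentence with Holm's procedure on the three confirmatory p-values: the smallest against exactly 0.05/3 (not rounded up to .017), the next against .025 and the largest against .05, stopping at the first non-rejection. Report .0167-level confidence intervals beside the unadjusted ones, because simultaneous intervals are less direct under Holm.

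Unless the statistical analysis plan already does so, add one sentence saying which p-value per outcome enters the procedure. An example is the GLMM used for sizing, with one adjusted model that includes the matching variables, exposure as at baseline, and the shape of time fixed before any outcome plots are drawn. Label the remaining analyses as sensitivity.

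The cost is about two sentences, with no extra participants, visits or data. The sample size can stay as it is, since sizing at 0.05/3 is conservative under Holm.
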